### 4.3 Exclusion Criteria

- Previous treatment for colorectal cancer in the metastatic setting with the exception that patients with urgent need of immediate treatment (high tumor load, symptoms) may have received one cycle of any FOLFOX regimen (no capecitabine!) in case of yet unconfirmed RAS status
- Previous EGFR-targeting therapy < 6 months after end of adjuvant therapy (previous chemoradiation for rectal cancer is accepted for inclusion into the trial and does not account as adjuvant therapy)
- Known brain metastases unless adequately treated (surgery or radiotherapy) with no evidence of progression and neurologically stable off anticonvulsants and steroids
- Chronic inflammatory bowel disease
- Peripheral neuropathy  $\geq$  NCI-CTCAE V 4.03 grade 2
- Other previous malignancies with the exception of a history of previous curatively treated basal cell carcinoma of the skin or pre-invasive carcinoma of the cervix or other curatively treated malignant disease without recurrence after at least 5 years of follow-up
- Significant disease that, in the investigator's opinion, would exclude the patient from the study
- History of cardiac disease; defined as:
  - Congestive heart failure > New York Heart Association (NYHA) class 2
  - Active coronary artery disease (myocardial infarction more than 6 months prior to start of study treatment is allowed)
  - Cardiac arrhythmias requiring anti-arrhythmic therapy (beta-blockers or digoxin are permitted)
  - Uncontrolled hypertension (defined as blood pressure  $\geq$  160 mmHg systolic and/or  $\geq$  90 mmHg diastolic on medication)
- Patients with interstitial lung disease, e.g., pneumonitis or pulmonary fibrosis or evidence of interstitial lung disease on baseline chest CT scan
- Known HIV, hepatitis B or C infection
- Known hypersensitivity reaction to any of the study components
- Radiotherapy, major surgery or any investigational drug 21 days before registration
- Pregnancy or lactation or planning to be pregnant during treatment and within 6 months after the end of treatment
- Subject (male or female) is not willing to use highly effective methods of contraception (per institutional standard) during treatment and for at least an additional 6 months after the end of treatment
- Known alcohol or drug abuse

- Any condition that is unstable or could jeopardize the safety of the patient and his compliance in the study

## 5 Schedule of Assessment and Procedures

Please refer to the study flow chart (page 11) for an overview.

Data will be collected via the completion of an electronic Case Report Form (eCRF) for each eligible patient. The investigator should confirm eligibility of the patient according to the inclusion and exclusion criteria of the study. All patients have to provide written Informed Consent before any study specific assessment is performed. A study specific assessment is defined as a procedure that is not part of the routine assessments performed for diagnostic purposes or standard care. Screening assessments should occur within 21 days of the first administration of induction therapy.

Patients not meeting the eligibility criteria will not be enrolled into the study. Patients should receive their first dose of study treatment as soon as possible after registration, but not later than 7 days after registration.

### 5.1 Study Assessments

#### 5.1.1 Tumor Assessments

Objective response will be evaluated based on RECIST criteria Version 1.1 (see Appendix 4) using CT scan or MRI scan. For patients with multiple measurable lesions, up to 5 lesions in total and 2 lesions per organ should be identified.

- If brain metastases are suspected or known, a CT or MRI scan of the brain will be performed. Patients with brain metastases are excluded.
- If suspicion of bone metastasis, a radiologic/ scintigraphic assessment should be performed

The exact technique used for measurement of lesions (i.e., either CT or MRI scan) will be left to the discretion of the investigator, however, for each patient the same technique must be used throughout the study, assessed whenever possible by the same individual. All lesions identified at screening have to be assessed at each scheduled tumor measurement. Patients with measurable lesions will be eligible for inclusion. Measurable lesions must have at least one diameter of 10 mm by CT scan (CT slice thickness no greater than 5 mm. When CT scans have slice thickness greater than 5 mm, the minimum size for a measurable lesion should be twice the slice thickness). Where there are several lesions, assessment is based on the sum of the longest diameters of the individual target lesions. Both – longest and shortest diameters should be recorded in the clinical report. Lymph nodes with a short axis of  $\geq 15$  mm are considered measurable and assessable as target lesions. The short axis measurement should

be included in the sum of lesions in calculation of tumor response. Nodes that shrink to  $< 10$  mm short axis are considered normal. All other pathological nodes (those with short axis  $\geq 10$  mm but  $< 15$  mm) should be considered non-target lesions.

In cases where there is suspicion of progression before the next scheduled assessment, an unscheduled tumor assessment should be performed.

In case a detected increase in tumor size is below the resolution limit of the CT/ MRI scanner, it is accepted to continue with treatment until a second assessment at a later time point unequivocally confirms progressive disease.

The following are defined as non-target lesions: bone lesions, leptomeningeal disease, pleural/pericardial effusion, ascites, inflammatory breast disease, lymphangitis, cystic lesions and lesions not measurable by computed tomography (CT) or magnetic resonance imaging (MRI). All non-target lesions are described over time and need not be measured.

The tumor assessment for inclusion should be recorded and measured within 21 days prior to treatment start of cycle 1. If a cycle of any FOLFOX regimen has been administered before enrolment due to urgent treatment need and yet unconfirmed RAS status this baseline CT / MRI must be performed before start of that cycle and still within 21 days prior to start of cycle 1. Please take care to avoid any delays within that tight schedule.

Tumor assessments will be performed 12 weeks after treatment start with induction therapy and every 8 weeks during maintenance therapy and re-induction. During the maintenance and re-induction period, disease assessments will be performed every 8 weeks, independent of chemotherapy cycle delay.

Please note that for subjects discontinuing maintenance or re-induction therapy prior to documentation of disease progression, tumor assessments will be performed at 8 week intervals (+/- 7 days) until disease progression is documented.

In order to assess progression during maintenance therapy, tumor assessments during maintenance will be compared to the tumor assessment performed at randomization (i.e., tumor assessment in week 12 of the study). In order to assess progression during re-induction, the tumor assessment at the start of re-induction therapy will serve as a reference (i.e., that tumor assessment showing progression during maintenance (1st progression)).

### 5.1.2 Other Clinical Assessments

- ECOG performance status

To be eligible for study entry, patients must have an ECOG performance score of 0 or 1. The patients' ECOG performance status will be assessed at the screening visit (within 7 days prior to treatment start), before every chemotherapy cycle during the treatment phase, at the EOT

visit that will take place 4 weeks after day 1 of the last chemotherapy cycle, and during follow-up.

- 12-lead ECG

A 12-lead ECG will be measured at screening. ECGs will only be performed during the treatment phase and for the EOT visit if clinically indicated.

- Physical examination

A physical examination will be performed at the screening visit, before start of each treatment cycle, at the EOT visit and at the FU visits (documentation of physical examination during follow up only until progression if treatment was discontinued before progression of disease occurred).

- Vital signs

Vital signs (blood pressure, heart rate, and body temperature) will be measured at the screening visit, before start of each treatment cycle and at the EOT visit. Body weight will be measured at the screening visit, before the start of each treatment cycle, at the EOT visit and for follow-up visits (documentation of body weight during follow up only until progression if treatment was discontinued before progression of disease occurred). Body height will be measured at screening only.

- Quality of life

Quality of life will be evaluated using the validated EORTC QLQ-C30, FACT-EGFRI 18, SKINDEX-16 and DLQI, which need to be filled out by the patient. Quality of life questionnaires will be completed at the following timepoints:

- Within 21 days before start of therapy (screening)
- Day 1 of 1st Induction cycle
- Day 1 of 2nd Induction cycle
- **Day 1 of every 2nd** following cycle, that is:
  - Induction cycle 4,
  - Induction cycle 6
  - Maintenance cycle 2 (Overall cycle 8)
  - Maintenance cycle 4 (Overall cycle 10)
  - etc., with ongoing two-cycles interval also when entering re-induction phase

Examples:

- Patient with 6 cycles maintenance is entering re-induction: QoL in re-induction Cycles 2, 4, 6, etc.
- Patient with 7 cycles maintenance is entering re-induction: QoL in re-induction cycles 1, 3, 5, etc.
- EOT visit

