| Confirming RAS status                  | X                                              |                                               |                                                                                                                                                                                  |                                                                                                    |                                                   |                         |
| Translational analyses                                     | x                                 |                                               |                                                                                                                                                                                  | x  (two timepoints)                                                                   | x                                    |                         |
| Quality of life                               | X                                              |                                               | day 1 of first and 2 nd cycle (week 2 & week 4),
After that day 1 of every 2 nd cycle (Cycle 4 [week 8], cycle 6
[week 12], cycle 8 [week 16], etc.) |                                                                                                    | X                                                 |                         |
| Concomitant medication                                     | X                                              |                                               | Continuous                                                                                                                                                                       |                                                                                                    |                                                   |                         |

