| Hematology                                                 | Within 2 days prior to each chemotherapy cycle: hemoglobin, erythrocytes, platelets, leukocytes, ANC                                                                                                                                                                                              |
| Clinical chemistry                                         | Within 2 days prior to each chemotherapy cycle: Sodium, potassium, calcium, magnesium, alkaline phosphatase, urea, AST, ALT, LDH, total bilirubin, albumin, creatinine, total protein, creatinine clearance (by Cockcroft-Gault formula)                                                          |
| Tumor Markers                                              | Carcinoembryonic antigen (CEA) and CA 19-9 after 6 cycles of induction therapy before randomization                                                                                                                                                                                               |
| Tumor measurement (CT or MRI)                              | 12 weeks after start of the induction therapy and every 8 weeks during maintenance and re-induction according to RECIST 1.1                                                                                                                                                                       |
| Quality of Life                                            | The EORTC QLQ-C30, FACT-EGFRI 18, Skindex-16, DLQI questionnaires will be completed on Day 1 of each chemotherapy cycle                                                                                                                                                                           |
| Translational analyses in serum and whole blood samples    | 
 
Optional at day 1 of cycle 1 and day 1 of maintenance therapy, investigational analyses, see section 5.1.5
 
Additionally, another optional blood sample set should be collected at the end of maintenance phase on day of PD diagnosis.
 
 |

If secondary resectability of metastasis is achieved, hepatic surgery is performed according to the standards of the respective institution, but should follow the published S1 guidelines of the German Cancer Society. A time interval of about 21 days between last chemotherapy application and surgery is recommended. These patients will have an End of Treatment visit

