Quality of life will be evaluated using the validated EORTC QLQ-C30, FACT-EGFRI 18, Skindex-16 and DLQI questionnaires. Data will be scored according to the algorithm described in the respective scoring manuals. For all quality of life domains and items, descriptive analyses will be presented stratified by visit and treatment arm.

Statistical comparison of quality of life between treatment arms may be distorted due to large quantities of missing questionnaires. Thus, the extent and process of missing data will be investigated. In case that data are missing completely at random, complete case analyses will be applied without biasing the results; otherwise treatment arms will be compared using longitudinal data modeling techniques.

For descriptive statistical analysis, summary tables will be provided showing measures of location and dispersion (minimum, quartiles, median, maximum, mean and standard deviation) stratified by visit and treatment arm. Furthermore, individual score items will be subjected to statistical analysis. Absolute changes of QoL-scores from baseline will be tabulated stratified by treatment group and visit. For graphical illustrations, Box-Whisker diagrams will be presented across visits for each treatment group.

For each domain, the proportion of patients in each arm with  $\geq 10$  points deterioration at each visit will be compared. It has been shown that this degree of change is perceptible and clinically significant on the 100 point scale. The numbers and percentages of patients with deterioration ( $\geq 10$  points deterioration), no change (less than 10 points deterioration/improvement) and improvements ( $\geq 10$  points improvement) will also be presented. Nonparametric (exact) Wilcoxon-Mann-Whitney tests will be applied for exploratory comparison purposes. In order to account for non-ignorable missing values due to death, progression or lost to follow-up, supplementary time profile analyses relative to baseline will be performed consisting of conditional descriptive analyses, given QoL-data up to a certain visit x, i.e. QoL tables at a specific visit x will be presented for patients with EOT-visit at or after visit x only.

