In addition, time-to-deterioration-analyses will be conducted for assessing any long term differences between treatment arms. Patients will be considered to have deteriorated for a given domain if a deterioration of at least 10 points on the 100 point scale is observed after randomization. Patients without deterioration will be censored at the time of the last QoL assessment. Kaplan-Meier methods will be used for associated data descriptions. For

comparison purposes, logrank tests will be applied. Additional details of the QoL analysis will be described in the SAP.

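### The quality-of-life schedules conflict on whether a form is taken at the start of maintenance, the reference score for deterioration after randomisation is not fixed, and the analysis method turns on an untestable missing-data condition

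*Protocol*

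**What the plan says.** **Schedule.** Protocol section 5.1.2 lists questionnaires at screening, on day 1 of induction cycles 1 and 2, and then at every second cycle. The entry after "Induction cycle 6" is "Maintenance cycle 2 (Overall cycle 8"). The flow chart follows the same pattern ("week 12], cycle 8 [week 16], etc"). Section 5.2.2, which covers the whole treatment phase, says instead that the "questionnaires will be completed on Day 1 of each chemotherapy cycle".

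**Reference score.** Section 8.4.3 (Quality of Life) states: "Absolute changes of QoL-scores from baseline will be tabulated stratified by treatment group and visit". It does not say which visit is baseline. For time to deterioration, a patient has an event if a "deterioration of at least 10 points on the 100 point scale is observed after randomization". The score from which the 10 points are counted is not named.

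**Missing data.** The same section first has the extent and process of missingness investigated. It then says: "In case that data are missing completely at random, complete case analyses will be applied without biasing the results"; otherwise longitudinal models are used. A later sentence introduces supplementary descriptive tables "In order to account for non-ignorable missing values due to death, progression or lost to follow-up".

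**The concern.** Health and skin-related quality of life is a secondary comparison between the maintenance arms, and tolerability is a large part of the case for or against continuing panitumumab. Randomisation comes after about 12 weeks of mFOLFOX6 plus panitumumab given to everyone. A change attributable to the maintenance arm has to be measured from a score taken after induction and before the first maintenance dose.

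The protocol leaves unclear whether the best-placed score is collected at all, and it does not say that the reference is re-set at randomisation. If the reference stays before induction, some of what is called deterioration after randomisation will be induction toxicity. In addition, choosing the comparison method by a finding that data are missing completely at random rests the analysis on something the data cannot show.

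**Working it through.** **1. The two schedules side by side.** Cycles last 14 days (section 3.1.1), so day 1 of overall cycle k falls nominally on day 14(k − 1) + 1.

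| Visit | Nominal day | 5.1.2 and flow chart | 5.2.2 |
|---|---|---|---|
| Induction cycle 6 (k = 6) | 14 × 5 + 1 = 71 | yes | yes |
| Maintenance cycle 1 (k = 7) | 14 × 6 + 1 = 85 | no | yes |
| Maintenance cycle 2 (k = 8) | 14 × 7 + 1 = 99 | yes | yes |

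Under 5.1.2 the gap is 99 − 71 = 28 days. The last form precedes the sixth induction dose, and the next comes 14 days into maintenance. Over the first 12 cycles, 5.1.2 gives 7 on-treatment forms (cycles 1, 2, 4, 6, 8, 10, 12) and 5.2.2 gives 12. The flow chart's week labels add to the confusion: it calls cycle 6 week 12, but only 10 weeks have elapsed on day 1 of that cycle.

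**2. Which baseline a reader would take.** Section 4.1 places the baseline tumour assessment before treatment start, and section 8.4.2 tabulates baseline characteristics for all enrolled patients. Both mean before induction. For tumour progression, section 5.1.1 explicitly re-sets the reference to the week-12 assessment at randomisation. Quality of life has no matching statement, so the natural reading is a pre-induction score.

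**3. What that reading does at a single visit.** The protocol gives no quality-of-life variability, so the following is assumed: SD 20, correlation 0.6 between visits, mean induction loss 0, 5 or 10 points, and an arm effect of 0 or −5 points. The SD of a change is 20 × √(2 × (1 − 0.6)) = 17.9. With mean change δ, P(change ≤ −10) = Φ((−10 − δ)/17.9).

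- Already 10 points below screening at randomisation: 29% (δ = 0), 39% (δ = −5), 50% (δ = −10).
- No arm effect: the proportions are equal in both arms whichever reference is used, so there is no bias.
- Arm effect −5, pre-randomisation reference: 39% against 29%, a difference of 10 percentage points.
- Arm effect −5, screening reference after a 10-point induction loss: 61% against 50%, a difference of 11 points.

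At a single visit the arm contrast survives. What changes is what the word deterioration means.

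**4. What it does to time to first deterioration.** Here early events use up the risk set. Assume a control median of 6 months, a true hazard ratio of 0.65 for new deterioration, a first form at 2 weeks (0.46 months), and a share p already worse in both arms and still worse at that form. New deterioration by the first form is:

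- control: 1 − exp(−0.1155 × 0.46) = 5.2%
- test: 1 − exp(−0.65 × 0.1155 × 0.46) = 3.4%

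The ratio is 0.66. With p = 0.40, the observed shares are 0.40 + 0.60 × 0.052 = 43.1% and 0.40 + 0.60 × 0.034 = 42.0%, a ratio of 0.98. The arm difference is almost hidden at that form.

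Simulation of the whole curve used 126 per arm (half of the 252 in section 8.2). The ranges cover differing assumptions about dropout and form timing:

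| Already worse at randomisation | Apparent hazard ratio |
|---|---|
| 0% | 0.64–0.65 |
| 20% | 0.72–0.74 |
| 40% | 0.77–0.82 |
| 60% | 0.81–0.89 |

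**5. The missing-data rule.** Observed data can contradict missing completely at random, for example when dropout depends on earlier scores. They cannot confirm it, because missingness may depend on the unseen score. The same section attributes missing values to death, progression and loss to follow-up and calls them non-ignorable. If that is right, the complete-case condition is not met; yet the branch stays available to whoever judges the condition satisfied.

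**The case against.** **A score near randomisation exists.** A reader might infer that nothing is measured at randomisation. That is untrue under 5.2.2, and even under 5.1.2 a score is taken at induction cycle 6, nominally 14 days before maintenance. Nor is screening the only pre-treatment form: day 1 of induction cycle 1 is also listed, although it too precedes any induction effect. This stands. The defect is the contradiction and the unnamed reference.

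**Complete-case analysis is not the default.** It is one branch of a conditional rule, with longitudinal models otherwise. Applied honestly, the rule probably leads to the longitudinal model. This stands too, and what remains is that the condition cannot be established.

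**Induction cannot bias the arms.** Randomisation follows induction, so its effects are balanced in expectation. Correct: the cost is dilution and blurred meaning.

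**The statistical analysis plan may settle it.** Section 8.4.3 defers further quality-of-life detail to that plan, which may name the baseline. If so, only the protocol wording needs aligning. The schedule conflict and the missing-data switch are written in the protocol itself and are not removed by that deferral.

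**The figures are invented and the endpoint is exploratory.** The protocol states no quality-of-life effect size or power, and section 8.4.1 makes all tests except the primary one exploratory. The hazard ratios above are therefore illustrations, and no loss of power is claimed because no target was set.

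**It is late to add a form.** This is version 9.0 of February 2021, and section 3.4 expects the last patient in around Q4 2020. A new questionnaire would reach few patients, which is why the remedy should rely on scores already collected.

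**Conclusion.** The point holds in three limited parts. First, 5.1.2 and the flow chart contradict 5.2.2 on whether a form is due at maintenance cycle 1. Second, section 8.4.3 does not fix the reference for change and deterioration after randomisation, and the protocol's usual sense of baseline is before induction. Third, the choice of method depends on a condition that data can reject but never confirm, and that conflicts with the section's own description of the missing values.

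The documents do not support the inference that the arm comparison is biased by induction. With no arm effect, both references give equal proportions in the two arms. The dilution of time to deterioration is real in direction if a pre-induction reference is used. Its size depends on the share already worse at randomisation, on that loss persisting to the first maintenance form, and on the assumed medians and dropout, none of which the protocol gives. The effect is confined to a secondary, exploratory endpoint.

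**What to change.** 1. Reconcile 5.1.2, 5.2.2 and the flow chart, including its week labels, into one questionnaire schedule.
2. For all between-arm analyses of change and time to deterioration, define the reference as the last questionnaire before the first maintenance dose: maintenance cycle 1 day 1 where collected, otherwise induction cycle 6, which both schedules require. Change from screening can still be tabulated to describe induction.
3. Make the longitudinal model on all available scores the main comparison unconditionally, and delete the missing-completely-at-random switch. The model still assumes missing at random, so keep the supplementary tables for non-ignorable missingness.

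The cost is protocol and analysis-plan wording and slightly more analysis work. Items 2 and 3 need no new data. Section 8.4.1 allows changes to the planned analysis to be justified and documented in the analysis plan before database lock.
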